6.3 Duration of Therapy

Treatment cycles will be repeated until progression or unacceptable toxicity occurs as previously described. Patients may also discontinue the drug in the following instances:

• Concomitant disease, which could, in the opinion of the investigator, affect patient safety, ability to comply with treatment, or primary study outcomes;

• Request by the patient through withdrawal of consent;

• The patient missed or did not follow up;

• The need for other antineoplastic therapy not specified in the protocol.

• If there are more than two response assessments, irinotecan therapy may be discontinued at the investigator's discretion.

6.4 Concomitant Therapy

No other treatment under approved antineoplastic research will be allowed during the study period, including chemotherapy, biological response modifiers, hormone therapy, immunotherapy, surgery or radiotherapy (except for single-dose radiation as a pain reliever). No other investigational drugs may be used during treatment in this protocol, and concomitant participation in another study is not allowed. If the patient requires radiation therapy while in the study, metformin may be discontinued one day before and resumed the day after radiation therapy.

Supportive care may include antiemetics to limit treatment-related nausea and vomiting, as well as loperamide for diarrhea. Anti-inflammatory drugs or narcotic analgesics may be offered as needed. Red cell concentrate or platelet transfusions should be administered as clinically indicated. The use of colony stimulating factors is allowed only in the case of neutropenic fever.

7. Schedule visits and evaluations

7.1 Before starting treatment

The following screening investigations are required two weeks prior to study initiation to assess patient eligibility:

• Signing of the Informed Consent Form

• Medical history, including diagnosis and treatment of mCRC (dose and duration), history of other diseases (active and resolved), concomitant diseases and medications, analgesic and demographic use.

• Complete physical examination, ECOG performance index (PS), body weight and height (screening only), and vital signs (ie temperature, blood pressure, heart rate, and respiratory rate).

• Pregnancy test: serum pregnancy test for all women of childbearing age and not in menopause.

• Hematological and blood biochemistry as described in section 7.4.

• Quality of life assessment using the EORTC QLQC30 questionnaire translated into Portuguese.

The following radiological examinations are required up to three weeks before starting the study drug:

• Abdominal computed tomography (CT) or nuclear magnetic resonance

(MRI) of the abdomen and chest tomography

• Other tests may be performed as directed by individual patient.

• Tumor response will be assessed at 6 weeks, 12 weeks, 18 weeks after initiation of therapy, and thereafter every 12 weeks until disease progression. The evaluation criteria performed by the researchers will follow the concepts proposed by RECIST v1.1.

7.2 During treatment

The following investigations are required during treatment:

• Medical assessment (including medical history, concomitant medications, analgesic use, adverse event assessment, physical examination, ECOG PS determination, vital signs, and body weight) on days 1 and 8 of cycle 1 and the first day of subsequent cycles.

• Biochemical, hematological analysis on days 1 and 8 of the first cycle and on the first day of subsequent cycles. If the patient has haematological, renal or hepatic toxicity ≥ grade 3, then laboratory tests should be repeated weekly until reduction to ≤ grade 1.

• Chest CT, total abdomen CT and chest X-ray will be performed during patient screening. If the patient has contraindications to the use of tomographic contrast, non-contrast-enhanced chest tomography and total abdomen magnetic resonance imaging will be performed. For response evaluation, tomography of the tumor sites will be performed every 6 weeks until the 18th week of the study, and then every 12 weeks. The same method and technique should be used to characterize each lesion identified and reported on baseline examination and during the study treatment period. Imaging-based evaluation, in addition to clinical examinations , are the techniques required when both can be used to evaluate the antitumor effect of treatment.

• Quality of life assessment with the EORTC QLQ-C30 and CR29 questionnaires translated into Portuguese will be performed on screening, on the first day of cycles 3, 6, 9, every four cycles onwards.

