|  | The primary endpoint is the disease control rate (stable disease + partial response + complete response) at the twelfth week of treatment. The efficacy assessment will be by intention of treatment. The metformin and irinotecan combination will be administered continuously until disease progression by RECIST v1.1 criteria or in case of severe toxicity or withdrawal of consent.  Sample size was calculated according to the optimal design of Simon. Considering a DCR of 13,2% on week 12 with placebo in third line, we believe that it would be clinically significant to increase this DCR to 26,7% .Considering an alpha error of 10% and a beta error of 20%, we planned to enroll 41 patients. This study would be considered positive if at least 9 patients had disease control on week 12.  This is a multi-institutional study, and it will take place at the Clinical Research Unit of Barretos Cancer Hospital.  Metformin will be given at a dose of 1500mg / day orally for 7 days, initially, and escalated to 2500mg / day if tolerated after one week of use, plus irinotecan at a dose of 125 mg per square meter body surface area D1 and D8 every 21 days. All patients will be treated until disease progression or appearance of prohibitive toxic effects. Those with a complete radiological response (CR) may discontinue irinotecan use two cycles after the diagnosis of CR (only if a total of six cycles is reached) at the investigator’s discretion, as well as those without presenting progression after two consecutive response assessments.  Tumor response will be assessed by computerized tomography (CT) or magnetic resonance imaging (MRI) every two cycles in the combined metformin and irinotecan phase and every twelve weeks during the metformin phase alone.  Toxic effects will be analyzed according to the National Cancer Institute Common Toxicity Criteria for Adverse Events, version 4 (NCI CTCAE v4). |
| Population | The target population includes adult patients with histologically confirmed or recurrent metastatic RCC refractory to treatment with oxaliplatin, irinotecan, fluoropyrimidine and an anti-EGFr agent if it is wild K-ras. |

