| Dose, treatment cycle | Metformin will be given at a dose of 1500mg/day (two pills in the morning at breakfast and one at dinner) for seven days. If there is no prohibitive adverse effect at 1500mg/day, the dose will be increased to 2500mg/day (three pills in the morning at breakfast and two at dinner), and this dose will be maintained until PD or unacceptable toxicity. Metformin will not be administered within two days prior to contrast infusion examinations at the discretion of the radiologist to minimize the risks of lactic acidosis.  Irinotecan will be administered at a dose of 125 mg/m² intravenously D1 and D8 every 21 days. |
| --- | --- |
| Preparation and administration | Metformin will have 500mg presentation. Not dosed by weight or body surface area. Irinotecan will be diluted in 5% dextrose solution. Its infusion will be performed intravenously, lasting 90 minutes. The irinotecan infusion will be preceded by the infusion of dexamethasone 20mg and ondansetrone 16mg. |
| Schedule of visits and evaluations | Study evaluations will be performed at the screening period (D-21 to D-1), the day of study initiation (D1), at D8 of the first cycle and at D1 of the subsequent cycles. |
| Effectiveness Assessments | Tumor assessment (CT or thoracic MRI, abdominal and pelvic) will be performed every 6 weeks until the 12^th^ week of initiation of treatment and after 12 weeks or at any time during the study where clinical progression is suspected. Any suspicion of progression due to clinical deterioration should be accompanied by radiological confirmation.  All images will be analyzed locally at the centers and this interpretation will be used for all clinical decisions. RECIST criteria will be used for primary endpoint analysis. |

1. Introduction

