| Hematologic | Keep the same  dose level | Maintain the same dose level *. | Discontinue the dose until the toxicity is ≤ 1 or has returned to baseline, then resume treatment at the same dose level ***. | Drop the dose until the toxicity is grade ≤ 1 or has returned to baseline, then reduce the dose to level 1 and resume treatment ^##^. |

* To start another cycle, the neutrophil count must be greater than 1,500 / mm ^3^, platelet count greater than 100,000 / mm ^3^and hemoglobin greater than or equal to 9 g / dL. ** Patients with grade 3 hypoglycemia, fatigue / asthenia who require more than 2 weeks without metformin administration to return to grade ≤ 1 toxicity should have their dose reduced to level -1.

*** Grade 3 lymphopenia and leukopenia do not require the dose to be suspended or reduced. Grade 3 recurrent neutropenia or thrombocytopenia that persists for at least 7 days requires dose reductions to level -1 in the next cycle.

Grade 4 haemorrhage requires discontinuation of study drug.

Grade 4 lymphopenia without other dose limiting events (opportunistic infection) does not require dose reduction.

If treatment discontinuation is required and the patient is unable to resume treatment within ≤ 28 days, treatment should be discontinued and the patient will continue to be followed for tumor response rate assessment and survival follow-up.

IRINOTECAN

Dose reduction in the patient will be allowed depending on the type and severity of the toxicity found. The dose levels of irinotecan are 125 mg / m², 100 mg / m² and 75 mg / m². The dose-limiting toxicities of irinotecan are related to neutropenia, alopecia, nausea, severe diarrhea, hypersensitivity reactions, asthenia and myalgia. Considering that the clinical toxicity most commonly related to irinotecan intolerance is diarrhea, the patient will be instructed to start treatment with loperamide when experiencing grade 1 diarrhea in order to avoid severe diarrhea and its complications.

| Toxicicity | Grade 1 | Grade 2 | Grade 3 | Grade 4 |
| --- | --- | --- | --- | --- |

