| Non haematological | Keep the same dose level | Reduce dose in 25 mg/m²and on the next cycle keep the same dose level | Hold the dose until the toxicity is ≤ 2, then resume treatment with a reduced dose of 25 mg / m² (minimum dose of 75 mg / m2) | Hold the dose until the toxicity is ≤ 1 or has returned to baseline, then reduce the dose by 50 mg / m² (minimum dose 75 mg / m2)  or discontinue treatment, at the discretion of the investigator |
| Haematological | Keep the same dose level | Reduce dose in 25 mg/m² and on the next cycle keep the same dose level | ² Hold the dose until the toxicity is ≤ 2, then resume treatment with a reduced dose of 25 mg / m² (minimum dose of 75 mg / m2) | Hold the dose until the toxicity is ≤ 1 or has returned to baseline, then reduce the dose by 50 mg / m² (minimum dose 75 mg / m2)  or discontinue treatment, at the discretion of the investigator |

 DOSE SCALE

Every effort should be made to reschedule the metformin dose to the starting dose level. This applies to any of the dose reductions due to haematological or non-haematological toxicities. The dose should be rescheduled if the following criteria are met at least one month after dose reduction:

• All non-haematological toxicities Grade ≥ 2 reach Grade ≤ 1

• All Grade ≥ 3 hematologic toxicities reach Grade ≤ 1

• Or, alternatively, all haematologic toxicities and non-haematologica Grade ≥ 3 are resolved to a Grade ≤ 2 or can be controlled with supportive therapy.

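### If irinotecan is given on D1 and D8, the protocol requires no blood count, biochemistry or medical assessment before D8 infusions from cycle 2 on, so the grade 3/4 hold has no required laboratory result to act on at those doses

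*Protocol*

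**What the plan says.** **Dosing.** The synopsis states the regimen twice. Under Study Design it is metformin "plus irinotecan at a dose of 125 mg per square meter body surface area D1 and D8 every 21 days"; under the dose and treatment cycle row, "Irinotecan will be administered at a dose of 125 mg/m² intravenously D1 and D8 every 21 days". Section 6.1 differs: 350 mg/m² on D1 only, every three weeks. Section 6.2 sides with the synopsis: "The dose levels of irinotecan are 125 mg / m², 100 mg / m² and 75 mg / m²", with reduction steps of 25 and 50 mg/m² and a floor of 75 mg/m².

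**Monitoring.** Section 7.2 asks for "Biochemical, hematological analysis on days 1 and 8 of the first cycle and on the first day of subsequent cycles", and sets the medical assessment on the same days. The synopsis visit row agrees: after screening and D1, evaluations fall "at D8 of the first cycle and at D1 of the subsequent cycles". Table 3 (section 7.4) has a Day 8 column for cycle 1 only and Day 1 columns for cycles 2 to 6. Its column for later cycles names no day, so section 7.2 and the synopsis fix D1 there.

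**Action rules.** The irinotecan table in section 6.2 says, for grade 3, "Hold the dose until the toxicity is ≤ 2, then resume treatment with a reduced dose of 25 mg / m²", and for grade 4, "Hold the dose until the toxicity is ≤ 1 or has returned to baseline, then reduce the dose by 50 mg / m²". Neither cell is limited to the start of a cycle. The grade 2 cells do refer to the next cycle, and it is unclear whether they act within one.

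**The concern.** A rule that withholds a drug on laboratory toxicity needs a laboratory result at the time of dosing. With D1/D8 dosing, the protocol supplies one before each D1 infusion and before the first D8 infusion, and then stops supplying it for D8.

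Section 6.2 puts neutropenia first in its list: "The dose-limiting toxicities of irinotecan are related to neutropenia". Section 6.4 restricts growth-factor support to febrile neutropenia, so a patient whose counts fall without fever depends on dose rules being triggered. A patient with new, symptom-free grade 3 or 4 neutropenia, or with a silent rise in creatinine or bilirubin, could reach D8 of cycle 2 or later and receive irinotecan at the current dose, up to 125 mg/m², when section 6.2 calls for a hold. Liver and kidney function also matter for metformin, since section 1.2 links lactic acidosis to impairment of either organ.

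Safety is a primary objective alongside disease control, but what is at stake here is protection of the individual patient, not the inference on disease control.

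**Working it through.** The protocol gives no figure to reproduce. The check sets planned infusion days against scheduled laboratory days.

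**Inputs**
- Infusions: D1 and D8 of each 21-day cycle (synopsis).
- Laboratory days: D1 and D8 of cycle 1, then D1 of each cycle (section 7.2, Table 3).
- Week 12 comes after four cycles (synopsis, Objectives).
- Planned enrolment: 41 (section 10.1).

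**Calendar to week 12.** D1 of cycle c is study day 21(c − 1) + 1, and D8 is seven days later.

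| Cycle | D1 | Test scheduled | D8 | Test scheduled |
|---|---|---|---|---|
| 1 | day 1 | yes | day 8 | yes |
| 2 | day 22 | yes | day 29 | no |
| 3 | day 43 | yes | day 50 | no |
| 4 | day 64 | yes | day 71 | no |

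**Formula.** Over c cycles there are 2c infusions and c + 1 laboratory days, each on an infusion day. Infusions without a scheduled test = 2c − (c + 1) = c − 1.
- 2 cycles (week 6): 1 of 4 = 25%.
- 4 cycles (week 12): 3 of 8 = 37.5%. At full dose this is 3 × 125 = 375 of 8 × 125 = 1,000 mg/m².
- 6 cycles: 5 of 12 = 41.7%.

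From cycle 2 on, scheduled tests are 21 days apart with one infusion in between.

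**Ceiling for the trial.** If all 41 patients received four full cycles, 41 × 3 = 123 infusions to week 12 would lack a scheduled test. These are untested infusions, not missed toxicities; the protocol gives no rate from which to estimate the latter.

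**Section 6.1 regimen.** One infusion per cycle on D1 and a test on every D1: 0 infusions without a test.

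**Do other provisions close the gap?**
- *Cycle-start threshold.* A footnote to the metformin table in section 6.2 requires neutrophils above 1,500/mm³, platelets above 100,000/mm³ and haemoglobin of at least 9 g/dL to begin another cycle. A patient at D8 should have met this a week earlier. It says nothing about a fall since then.
- *Weekly repeat tests.* Section 7.2 requires them once haematological, renal or hepatic toxicity of grade 3 or worse is known. If found on D1, they would cover the following D8. They cannot find a new event.
- *Cycle 1 D8 test.* Patients with early toxicity are identified and their dose reduced. Toxicity first arising in cycle 2 or later is not covered.
- *Attendance for the infusion.* Symptoms can be noticed and graded, although no assessment is scheduled. Silent laboratory changes cannot.

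What remains uncovered is new, asymptomatic laboratory toxicity arising between D1 and D8 from cycle 2 on.

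**The case against.** The strongest objection is that this follows from a different error. Section 6.1 is the section on drug administration, and it gives irinotecan on D1 only. The single D8 visit in cycle 1 does not show that D8 irinotecan was intended, because section 6.2 needs it for the metformin escalation decision. On that reading the schedule in section 7.2 and Table 3 is complete. This stands as a condition on the finding. It does not dispose of it, because the synopsis states D1/D8 dosing twice and the irinotecan dose levels and steps in section 6.2 fit that regimen, not 350 mg/m².

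A second objection is that the other safeguards are substantial: patients pass a count threshold at D1, cycle 1 screens out early toxicity, and known grade 3 or worse toxicity brings weekly tests. That narrows the population at risk considerably, and it would be wrong to infer that the hold and reduction rules are the only protection before fever. The gap is narrower for it but still open.

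A reader might also infer that the hold cannot be applied at D8 at all. The protocol does not support that: it lists required tests and forbids none, so a site may run a count under local practice. The accurate statement is that no protocol-required result supports the hold.

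Finally, the ceiling of 123 is not a forecast. The protocol works with week-12 disease control of 13.2% to 26.7%, treats until progression, enrols only 17 patients in the first stage and allows irinotecan to be stopped in some non-progressing patients. Actual exposure would be lower. The per-patient fraction is the more useful figure.

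**Conclusion.** The point holds, conditionally. If the synopsis regimen governs, 3 of 8 planned irinotecan infusions per patient to week 12, and every second infusion from cycle 2 on, come with no required blood count, biochemistry or medical assessment. The grade 3/4 hold then has no protocol-required laboratory result to act on at those doses. If section 6.1 governs, the number is 0.

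The conclusion rests on the regimen being D1/D8, on the hold cells applying to any dose (they are not restricted to D1), and on sites doing no more than the protocol requires. The clinical consequence cannot be quantified, because the document gives no rate for new silent toxicity between D1 and D8.

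It should not be read as a threat to the efficacy result: the disease control endpoint, the sample size of 41 and the design error rates do not depend on it. It is a patient-safety correction that should be made together with the regimen conflict.

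**What to change.** First settle which irinotecan regimen applies, and make the synopsis, section 6.1 and section 6.2 agree.

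If D8 dosing is kept:
- Require a blood count, biochemistry and toxicity grading before every D8 infusion, in the synopsis visit row, in section 7.2 and in Table 3 (a Day 8 column for cycles 2 onward).
- State in the irinotecan table of section 6.2 that it applies to D8 doses, and whether the grade 2 reduction acts within the cycle or from the next one.

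All 8 of 8 infusions to week 12 would then have a same-day test, against 5 of 8 now.

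The cost is protocol wording, one table column, and one routine blood draw with a brief toxicity check per D8 infusion, on a day when the patient already attends. That is 3 extra draws per patient over four cycles, at most 123 for 41 patients.

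If D1-only dosing is kept, the laboratory and visit schedule needs no change on this account.

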7.3 After the end of treatment (follow up)

• Medical (including medical history, concomitant medications, analgesic use, physical exams, ECOG PS determination, vital signs and body weight) and laboratory evaluation will be performed 28 days after protocol exclusion. Patients withdrawn from the study will be followed for survival assessment.

7.4 Study Summary

Table 3 Visit Evaluation Schedule

| Required Investigations | Tracking | Day  1  Cycle  1 | Day  8th  Cycle  1 | Day  1  Cycle  2 | Day  1  Cycle  3 | Day  1  Cycle  4 | Day  1  Cycle  5th | Day  1  Cycle 6 | Subsequent cycles | End of treatment |
| --- | --- | --- | --- | --- | --- | --- | --- | --- | --- | --- |
| Medical evaluation |  |  |  |  |  |  |  |  |  |  |
| Clinical symptoms | X | X | X | X | X | X | X | X | X | X |
| Physical exam | X | X | X | X | X | X | X | X | X | X |
| Vital signs, body weight and PS | X | X | X | X | X | X | X | X | X | X |
| Concomitant Drugs | X | X | X | X | X | X | X | X | X | X |
| Adverse Event Assessment | X | X | X | X | X | X | X | X | X | X |
| Hematology |  |  |  |  |  |  |  |  |  |  |
| Blood count  Complete | X | X | X | X | X | X | X | X | X | X |
| Biochemistry |  |  |  |  |  |  |  |  |  |  |
| Creatinine / Urea / Glucose | X | X | X | X | X | X | X | X | X | X |
| AST / ALT / bilirubin / alkaline phosphatase / cholesterol and triglyceride levels | X | X | X | X | X | X | X | X | X | X |
| Insulin, CEA, whole blood | X | X | X | X | X | X | X | X | X | X |
| Sodium, Potassium, Magnesium, Calcium,  phosphor | X | X | X | X | X | X | X | X | X | X |
| Radiology ^*^ |  |  |  |  |  |  |  |  |  |  |
| Chest / abdomen CT | X |  |  |  | X |  | X |  |  |  |
| Quality of life assessment | X |  |  |  | X |  |  | X | X | X |
| Pregnancy test | X |  |  |  |  |  |  |  |  |  |

Chest CT, total abdomen CT will be performed during patient screening. For evaluation of response will be performed tomography of the tumor sites and chest X-ray at 6 weeks, 12 weeks and every 12 weeks onwards.

8. Evaluation Criteria

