This study will be conducted in Barretos Cancer Hospital. The tumor response will be evaluated in the sequence below, counting from the first day of medication infusion: 6th week, 12th week, 18th week, 24th week and every 12 weeks after, using consistent imaging techniques (CT) or MRI if patients are contraindicated for CT. The evaluation will be made by the researchers through RECIST v1.1. Discontinuation of metformin medication for three days prior to three days after infusion of any iodinated contrast media for radiological studies will be allowed at the discretion of the radiology team. This frequency of examinations is similar to that used in third-line mCRC clinical studies and arises from the need to follow more closely patients whose disease has more aggressive behavior and a greater chance of disease progression in the first few years.

Toxic effects will be analyzed according to NCI CTCAE version 4.0. (73)

The study period for each patient is defined as the day of patient inclusion until:

• The day when an event (disease progression as defined by RECIST, or death) is observed.

• The day when the patient discontinues treatment due to an unacceptable adverse event, withdrawal of consent or discontinuation of the study, or for any other reason than 21 days.

All those who discontinue treatment for any reason will be followed for survival assessment.

Patients who demonstrate disease progression during the study or who discontinue the study drug for any reason other than disease progression and withdrawal of consent (ie adverse event, administrative reasons, etc.) will be subjected to survival monitoring. The investigator or designated member will contact the patient monthly for survival information and additional antineoplastic therapies.

6. Therapeutic regimens, expected toxicity, dose modifications.

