Progressive Disease (PD): an increase of at least 20% in the sum of LD of the measured lesions with reference to the lowest LD sum recorded since the beginning of treatment. The appearance of new lesions will also constitute progressive disease. Under exceptional circumstances, evident progression of non-target lesions may be accepted as evidence of disease progression.

Criteria for radiological response assessment

| Target Injuries | Non Target Injuries | New Injuries | answer  General | The best answer for this category also requires |
| --- | --- | --- | --- | --- |
| CR | CR | Not | CR | > 4 weeks confirmation |
| CR | Non-CR / Non-PD | Not | PR | > 4 weeks confirmation |
| PR | Non-PD | Not | PR |  |
| SD | Non-PD | Not | SD | Documented at least once > 4 weeks from baseline |
| PD | Any | Yes or no | PD | Not before SD, PR or CR |
| Any | PD * | Yes or no | PD |  |
| Any | Any | Yes | PD |  |
| * In exceptional circumstances, evident progression of non-target lesions may be accepted as evidence of disease progression.  Note :  Patients with a general deterioration of health require discontinuation of treatment without objective evidence of disease progression which at that time should be reported as "symptomatic deterioration". Every effort should be made to document objective progression even after treatment discontinuation. | | | | |

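### The protocol gives two different imaging fields for the response scans, and the narrower one can hide new lesions and raise the week-12 DCR; the scan calendars also conflict after week 12

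*Protocol*

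**What the plan says.** **Coverage of response scans.**
- Section 7.2: after chest and total abdomen CT at screening, "tomography of the tumor sites will be performed every 6 weeks until the 18th week of the study, and then every 12 weeks". Chest X-ray is listed here for screening only.
- Section 7.4, note to Table 3: "tomography of the tumor sites and chest X-ray at 6 weeks, 12 weeks and every 12 weeks onwards". Only this note puts a chest X-ray at response visits.
- Section 7.4, Table 3 itself: the row above that note marks chest and abdomen CT at screening, cycle 3 day 1 and cycle 5 day 1.
- Synopsis, Effectiveness Assessments: "Tumor assessment (CT or thoracic MRI, abdominal and pelvic) will be performed every 6 weeks" up to week 12.

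**Progression.** Appendix 2 states: "The appearance of new lesions will also constitute progressive disease". Section 3.3.2 says the same.

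**Calendar.**
- Section 5: "6th week, 12th week, 18th week, 24th week and every 12 weeks after", counted from the first infusion.
- Section 7.1: "Tumor response will be assessed at 6 weeks, 12 weeks, 18 weeks after initiation of therapy, and thereafter every 12 weeks until disease progression". Section 7.2 agrees with it.
- Table 3 note: weeks 6 and 12, then every 12 weeks. The synopsis row on effectiveness assessments reads the same way.
- Synopsis, Study Design: "every two cycles in the combined metformin and irinotecan phase and every twelve weeks during the metformin phase alone".

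**Decision rule (section 10.1).** Null DCR 13.2%, target 26.7%, alpha 10%, beta 20%, 41 patients, positive if at least 9 have disease control at week 12.

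**The concern.** Disease control counts stable disease. A patient whose known lesions are stable but who has a new lesion elsewhere has progressed; if the scan does not cover that region, the patient is scored as a success. The error runs in one direction only. The trial has one arm, images are read locally, and the result is set against a fixed outside figure of 13.2%, so nothing in the design offsets it. The requirement in section 7.2 to keep the same method and technique applies to lesions identified and reported at baseline, so it does not secure the detection of new ones. An analysis plan cannot repair this later, because a region that was never imaged cannot be read.

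The calendar conflict is a second and lesser matter. PFS and duration of response are dated by the scan that shows progression. If sites follow different sections, the same disease course receives different dates.

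**Working it through.** **1. The plan's own figure.** With X the number of patients with disease control, X ~ Binomial(41, p), the exact single-stage values are:
- P(X ≥ 9 | p = 0.132) = 0.083, against a stated alpha of 10%;
- P(X ≥ 9 | p = 0.267) = 0.804, against a stated power of 80%.

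The rule reproduces.

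**2. Sensitivity to hidden progression.** Let d be the share of all patients whose week-12 progression is read as stable because the new lesion lies outside the imaged field. At a true DCR of 13.2%, the apparent DCR is q = 0.132 + d, and the chance of a false positive is P(X ≥ 9 | 41, q). The documents give no value for d; the range is assumed.

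| Hidden per 100 patients | Apparent null DCR q | P(X ≥ 9 of 41) |
| --- | --- | --- |
| 0 | 0.132 | 0.083 |
| 1 | 0.142 | 0.118 |
| 2 | 0.152 | 0.161 |
| 3 | 0.162 | 0.210 |
| 5 | 0.182 | 0.325 |

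If the share m is taken of progressors instead, q = 0.132 + 0.868 × m. Then m = 1%, 2%, 3% and 5% give 0.113, 0.149, 0.190 and 0.285.

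The trial is described as two-stage, with 17 patients first (section 18), but the protocol states no first-stage boundary. With an assumed stop at 2 or fewer of 17, the chance of a false positive is 0.072 with nothing hidden, and 0.098, 0.130, 0.166 and 0.252 at those same values of m. The levels are lower and the pattern is the same.

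**3. Scan weeks implied by each section.**

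| Source | Weeks |
| --- | --- |
| 7.1 and 7.2 | 6, 12, 18, 30, 42 |
| Table 3 note (and synopsis, Effectiveness Assessments, as read) | 6, 12, 24, 36, 48 |
| Section 5 | 6, 12, 18, 24, 36, 48 |
| Synopsis, Study Design, while on the combination | 6, 12, 18, 24, 30, 36, 42, 48 |

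A progression just after week 12 is found at week 18 or at week 24; one just after week 18 is found at week 24 or at week 30. The gap is 6 weeks in each case.

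**4. Cycles against weeks.** On 21-day cycles without delay, cycle 3 day 1 falls 2 × 3 = 6 weeks after the start and cycle 5 day 1 falls 4 × 3 = 12 weeks after it, so Table 3 agrees with the week-based text. Section 6.2 allows up to 3 weeks for recovery from toxicity, and 28 days in a footnote to its dose table. If a cycle start slips by 3 weeks, a scan tied to cycle 5 falls at week 12 + 3 = 15, while section 5, counting from first infusion, still places it at week 12.

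**The case against.** The strongest reply is that the wider coverage is already in the protocol. The Table 3 row requires chest and abdomen CT at exactly the two visits that decide the primary endpoint, the synopsis names thorax, abdomen and pelvis, and Appendix 2 sets CT technique for all three regions. Imaging is also required whenever clinical progression is suspected. To count as an error, a patient would need a new lesion outside the field, no progression within it and no clinical suspicion, at a site that followed the narrower wording. This stands in part: the protocol contradicts itself and has not settled on narrow imaging, and the miss rate is unknown. It does not remove the defect, because section 7.2 and the Table 3 note are procedural text that a site would follow, and both contrast full screening imaging with tumour sites at response.

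A reader might infer three stronger things that the documents do not support.
- **That the calendar conflict biases the primary endpoint.** Every week-based version includes weeks 6 and 12. Only cycle-tied timing can drift, and only if cycles are delayed.
- **That stopping irinotecan at the investigator's discretion moves the week-12 scan.** The synopsis allows this after a complete response only once six cycles are reached (6 × 3 = 18 weeks), or after two consecutive assessments without progression, hence after the week-12 scan. Section 6.3 asks for more than two assessments.
- **That PFS will be tested against historical data.** Section 12 plans Kaplan-Meier estimation and names no such comparison.

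**Conclusion.** The point holds as an internal contradiction with a possible effect on the primary endpoint. Followed literally, the narrower coverage can only raise the week-12 DCR. The decision rule has little room for this: hidden progression in 1 of every 100 patients takes the single-stage chance of a false positive from 0.083 to 0.118, above the stated 10%. The figures of 0.210 and 0.325 belong to assumed rates of 3 and 5 per 100. They show sensitivity and do not estimate what will happen.

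The calendar conflict is real but secondary. It can shift PFS and response-duration dates by about 6 weeks. It leaves the week-12 endpoint alone, apart from the drift that cycle-based timing allows when cycles are delayed. Under the Study Design text of the synopsis, stopping irinotecan also lengthens the later scan interval to 12 weeks, so a treatment decision alters how progression is ascertained after week 12.

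**What to change.** 1. In section 7.2 and the Table 3 note, replace the tumour-site wording, and the chest X-ray in the note, with the coverage the synopsis already gives: chest, abdomen and pelvis at every response assessment, by the same modality as at baseline.
2. State the same coverage for screening in sections 7.1, 7.2 and 7.4, and align the Table 3 row. These sections now name chest and abdomen but not the pelvis, so a mere reference to baseline coverage would not bring it in.
3. Reconcile both synopsis rows, section 5, section 7.1, section 7.2 and the Table 3 note to one calendar in weeks from the first infusion. It should not move with cycle delays or with stopping irinotecan. Table 3 should label its scans by week and show those after week 12.

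The cost is an amendment to wording and a slightly larger scan field wherever the narrower text was being followed. Sample size and decision rule are unchanged.
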